#### 2.10.2. Statistical Analysis for Secondary Outcomes

The POMS questionnaire (taken before bedtime in each intervention) will be analyzed using repeated-measures ANOVA to assess the differences between interventions (followed by the Tukey HSD post hoc tests if necessary) and paired samples *t*-tests to evaluate the effect of each intervention separately against the baseline measures. 

The LFPQ will be administered twice, before and after an ad libitum meal on day 2. The paired samples *t*-tests will be computed for each intervention separately to assess the pre-post differences and the differences between the baseline and intervention measurements. A repeated-measures ANOVA will also be computed on the delta (post-pre LFPQ scores) to compare the score differences between interventions. Tukey’s HSD post hoc tests will be performed if significance is reached. Similarly, the food intake during the ad libitum meal will be analyzed using repeated-measures ANOVA (interventions comparisons) and the paired samples *t*-tests (the baseline-intervention comparisons). 

For the Karolinska, ROF, and hunger sensation scale, several measures throughout the day will be taken. In order to assess the time course of these measures for each day, the area under the curve (AUC) for each questionnaire will be calculated using the trapezoid method and analyzed using repeated-measures ANOVA for the differences between the interventions and using the paired samples *t*-tests for the baseline-intervention comparisons.

Manipulation checks will be performed (paired samples *t*-tests) on the energy balance measure between each energy deficit session to ensure that the induced energy deficit was isocaloric.

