### 1.2. Aims

The main objective of this study is to evaluate the acute effect of a moderate energy deficit (500 kcal) induced by diet, exercise, or both (mixed: −250 kcal by diet and 250 kcal by exercise) on the quality and architecture of sleep in healthy young adults. The secondary objectives will be to investigate the effect of the energy deficit modality on (i) next morning appetitive responses ([i_a_] ad libitum food intake, [i_b_] appetite sensations, [i_c_] food reward, (ii) sleepiness, and (iii) fatigue.

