
### 2.5. Experimental Sessions

#### 2.5.1. Control Session

The control session (CTL) will be carried out over 28 h and starts when the participant wakes up (6:45 a.m.). Upon waking up, the participants will be equipped with accelerometers (GT3X+, ActiGraph LLC, Pensacola, FL, USA) on their waists until the next morning to monitor their physical activity. They will be asked to maintain their habitual overall level of physical activity, and any structured physical exercise during and 48 h before the session will be prohibited. Food intake will be organized over three scheduled meals (breakfast (7:15), lunch (12:30), and dinner (20:00)). The meals offered will be adapted to each participant’s preferences based on a panel of dishes proposed by the investigators (Table S2). The participants will be asked to take pictures of every consumed meal (habitual meal) and to fill out a food diary by weighing each consumed food item using a kitchen scale (EBC9i, EssentielB, Fretin, France) provided by the investigators. Appetite, sleepiness, and fatigue will be assessed throughout the day (i.e., 12 measures; Figure 2) using the Karolinska Sleepiness Scale (KSS) [33], Rating-of-Fatigue Scale (ROF) [34] and appetite visual analogue scale (VAS; 150 mm) [35], respectively. The Profile of Mood States questionnaire (POMS) [36] will be completed before bedtime. During the night, sleep will be measured by ambulatory polysomnography. The next morning, the participants will be asked to return to the laboratory in a fasting state. They will complete the Leeds Food Preference Questionnaire (LFPQ) [37,38] on a computer before being served a standardized ad libitum meal (buffet-style meal). After the meal, they will complete the LFPQ a second time. Sleepiness, fatigue, and appetite will be assessed throughout the morning (i.e., 8 measures; Figure 1). The control session will end at 10:35. 

The data collected during the control session will be used to assess the energy balance of each subject and to calibrate the food intake and exercises of the energy deficit sessions.

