#### 2.7.2. Experimental Secondary Outcomes

Other sleep outcomes: Beyond SE, the Sleep Profiler-PSG2 provides other sleep variables, such as the following: total sleep time (TST); sleep onset latency (SOL); wake after sleep onset (WASO); the number of awakenings lasting more than 30 s; the arousal index and staging (time spent in non-rapid (NREM; Stage-1, Stage-2, and Stage-3) and rapid eye movement (REM)), according to the American Academy of Sleep Medicine recommendations [43].Mood: The Profile of Mood States will be used to assess the participant’s mood before the night of each experimental session [36]. All participants will be asked to rate “How are you feeling right now?” using 24 mood descriptors (e.g., nervous, unhappy, etc.). For each descriptor, the participants have to answer using a 5-point Likert scale, from 0 (not at all) to 4 (extremely). This questionnaire is divided into six subscales (fatigue, confusion, vigor, depression, tension, and anger), each containing four mood descriptors.Ad libitum energy intake: A standardized buffet breakfast will be organized on day1 of each session [44]. Consumed food items will be weighed and recorded by the investigators. Subsequently, the computerized nutrient analysis software (Bilnut 4.0 SCDA, Nutrisoft) and Ciqual tables (2020 version) will calculate the energy intake and the part of energy derived from each class of macronutrients.Food liking and wanting: LFPQ will be used to assess the individual’s food preferences [37]. It comprises two sub-tasks that require interactions from the participant. The first task (explicit task) involves an explicit assessment of food pictures using the 100-unit VAS. Single food images are randomly displayed to the participant on a screen computer, who is required to rate it according to “How pleasant would it be to taste some of this food now?” (explicit liking) and “How much do you want some of this food now?” (explicit wanting). The second task (implicit or forced choice task) requires a quick choice to be made between paired combinations of food pictures from different categories. During this task, a series of food image pairs are presented to the participant with the instruction, “Which food do you most want to eat now?”.Appetite sensations: Sensations of hunger, appetite, and a desire to eat will be measured using a VAS (150 mm) throughout all sessions (i.e., 9 measures on day 0, and 8 measures on day 1). These VASs were previously validated by Flint et al. (2000) [35].Sleepiness: The subjective level of sleepiness will be measured using the KSS [33]. The participant has to rate his subjective sensation of sleepiness in the last 10 min using a 9-point scale, ranging from 1 (extremely alert) to 9 (extremely sleepy).Fatigue: The French-validated version of the ROF scale will be used to assess the state of fatigue [34]. This is an 11-point scale, from 0 (not fatigued at all) to 10 (total fatigue and exhaustion), with accompanying descriptors and schematic components, which allow for tracking perceived fatigue across different ranges of daily life, physical activity, and recovery contexts.

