#### 2.10.1. Statistical Analysis for Sleep Outcomes

For the sleep outcomes (TST, SOL, SE, WASO, REM, N1, N2, N3, and arousals), the differences between interventions (EED, MED, and DED) will be assessed using a repeated-measures ANOVA by comparing the three interventions as a within-subject factor. If significance is obtained, post hoc pairwise comparison tests with a Tukey HSD correction will be applied. Sleep measures during the interventions will also be compared to the baseline to evaluate the effect of each intervention separately, using paired samples *t*-tests. The effect sizes will be computed to assess the strength of the relationships: Cohen’s d for the *t*-tests and eta^2^ for the main effects.

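### The only head-to-head test of food reward between the three deficit modalities uses the change across the ad libitum meal, so the part of a modality effect that is equal before and after eating drops out

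*Protocol article*

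**What the plan says.** Section 1.2 of the Protocol article sets the objective: "The secondary objectives will be to investigate the effect of the energy deficit modality on (i) next morning appetitive responses". Food reward is listed as one of those responses, (i_c). Section 2.7.2 names the instrument: "LFPQ will be used to assess the individual’s food preferences". It yields explicit liking, explicit wanting and a forced-choice task.

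Section 2.5.1 has participants arrive fasting and complete the LFPQ "on a computer before being served a standardized ad libitum meal (buffet-style meal"), then complete it again after eating. Section 2.5.2 runs the deficit sessions in the same way.

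Section 2.10.2 plans three LFPQ analyses. The first two are paired t-tests "for each intervention separately to assess the pre-post differences and the differences between the baseline and intervention measurements". The third is the ANOVA: "A repeated-measures ANOVA will also be computed on the delta (post-pre LFPQ scores) to compare the score differences between interventions", followed by Tukey post hoc tests if significant. Section 2.10.1 shows which sessions count as interventions: "the differences between interventions (EED, MED, and DED) will be assessed using a repeated-measures ANOVA". The control session is not among them.

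**The concern.** The objective asks whether the way the deficit is produced changes food reward the next morning. Suppose one modality raises wanting in the fasting state and the rise is still there after breakfast. That is a modality effect on food reward by any ordinary reading of the objective. The delta removes it, because the same amount is subtracted from itself.

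The delta has a second difficulty. It is taken across a meal of free size, and the amount eaten is listed in the same objective as a response that modality may alter. A difference in delta could come from a difference in reward, a difference in intake, or both.

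At stake is a null result on food reward that says little about fasting liking and wanting, or a positive one that is hard to interpret. Section 3 gives food reward particular emphasis among the compensatory responses, so readers will look for this comparison.

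**Working it through.** **The plan's own figure.** The article states a sample size only for sleep efficiency (section 2.2.1): four measures, f = 0.25, correlation 0.5, alpha 0.05, sphericity correction 1, 80% power. With noncentrality λ = f²·n·m/(1 − ρ), n = 24 gives λ = 0.0625 × 24 × 4 / 0.5 = 12 on 3 and 69 degrees of freedom, and power 0.817. With n = 23 the power is 0.797. So 24 reproduces. No corresponding figure exists for the LFPQ, and the point below does not depend on this one.

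**Which test compares what (section 2.10.2).**

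| LFPQ analysis | Comparison | EED, MED and DED against each other? |
|---|---|---|
| Paired t-test, pre vs post | within one session | no |
| Paired t-test vs baseline | one modality vs control | no |
| Repeated-measures ANOVA | three modalities, on post − pre | yes, on the delta only |

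Other outcomes in the section are treated differently. POMS and ad libitum intake are compared between modalities on the value itself, and the repeated rating scales on their area under the curve. Only the LFPQ is reduced to a change score for this purpose.

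**What the delta carries.** Let modality k shift the pre-meal score by a_k and the post-meal score by b_k. The delta is shifted by b_k − a_k. If b_k = a_k, the shift is zero. If half persists (b_k = a_k/2), the delta shows −a_k/2. If none persists (b_k = 0), it shows −a_k, the full size with the sign reversed. This is algebra and needs no assumption about variances.

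**Illustrative size.** These assumptions are not in the article: score SD 1; between-session correlation of the same score 0.5; same-session pre/post correlation 0.75; cross-session pre/post correlation 0.5; modality effects d, d/2 and 0. The error variance for a between-session comparison is then 1 − 0.5 = 0.5 for the pre-meal score. For the delta it is 2(1 − 0.75 − 0.5 + 0.5) = 0.5, the same.

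The effects d, d/2 and 0 have a sum of squares about their mean of d²/2. For the pre-meal score, λ = 24 × (d²/2)/0.5 = 24d², with 2 and 46 degrees of freedom. For the delta, λ = 24d²(1 − p)², where p is the fraction of the shift still present after the meal.

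- d = 0.5: pre-meal λ = 6. Delta λ = 0, 1.5 and 6 for p = 1, 0.5 and 0.
- d = 0.8: pre-meal λ = 15.36. Delta λ = 0, 3.84 and 15.36.

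Power, from 20,000 simulated trials per row with n = 24 and three modalities:

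| d (SD) | fraction persisting | pre-meal score | delta |
|---|---|---|---|
| 0.5 | 1 | 56% | 5% |
| 0.5 | 0.5 | 55% | 17% |
| 0.5 | 0 | 55% | 56% |
| 0.8 | 1 | 93% | 5% |
| 0.8 | 0.5 | 94% | 38% |
| 0.8 | 0 | 93% | 93% |

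The noncentral F distribution gives the same to within a percentage point: 55.5% and 93.4% on the pre-meal score; 17.0% and 37.8% on the delta at half persistence.

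**The case against.** **Levels are not wholly untested.** The t-tests against baseline most naturally read as tests on the scores themselves. A shift from control that outlasts the meal would then be visible, and an effect against control is part of what the objective asks. This stands, and it is why the objective is partly tested rather than untested. It does not close the gap. If one modality differs significantly from control and another does not, that is no test of the difference between them. Section 2.1 also places the control session before the randomised ones, so those contrasts carry any order effect. The delta ANOVA remains the only randomised comparison of food reward.

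**The delta is a legitimate quantity.** Measuring before and after a meal makes the change in reward with eating a coherent target, and nowhere does the article say that the fasting score is the intended endpoint. This also stands. But section 1.2 does not define food reward as a change across a meal either, and the delta alone answers the narrower question.

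**The full plan may say more.** A condensed article can leave detail out. Here, however, it states the between-modality analysis positively, and section 2.10.4 has further analyses reported as non-planned.

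**Stronger readings that the document does not support.** A reader might infer that the delta cancels every modality effect seen at both times; only the equal component cancels. A reader might also infer that the delta is inherently noisier, or that a fixed multiple of the sample size is lost. The error-variance ratio of delta to pre-meal score is 2(1 − r − ρ + c)/(1 − ρ), with r the same-session pre/post correlation, ρ the between-session correlation and c the cross-session pre/post correlation. None of the three is given for the LFPQ, so no general penalty can be stated. Nor does the article show that a delta difference would be due to intake; that is only a possibility, and intake is itself compared between modalities in the same section.

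**Conclusion.** The point holds in a limited form. Food reward is compared head to head between EED, MED and DED only on the post-minus-pre LFPQ change. That comparison cannot see the part of a modality effect common to both time points, and it is taken across a meal whose size modality may alter. Objective (i_c) is partly addressed by the tests against control, but the randomised comparison of fasting food reward is absent from the stated analyses.

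The cancellation is certain; its practical size is not. Under the assumed correlations it ranges from no loss, when nothing persists after the meal, to power at the alpha level, when the shift persists in full. This is a secondary outcome and the priority is low, but the correction is easy.

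**What to change.** In section 2.10.2, pre-specify a repeated-measures ANOVA across EED, MED and DED on the pre-meal LFPQ score, with the same Tukey post hoc tests as the other outcomes. Keep the ANOVA on the delta, describe it as the analysis of the reward response to eating, and interpret it alongside ad libitum intake.

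The cost is a sentence in the plan and an additional model per LFPQ scale, on data already collected. The downside is one more secondary test for each scale. Specifying it before the data are analysed avoids having to report it later as non-planned under section 2.10.4.

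### The day-1 appetite AUC pools ratings from before and after the ad libitum buffet, so it can dilute or offset a difference in fasting appetite

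*Protocol article*

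**What the plan says.** Section 2.10.2 of the protocol article fixes the summary measure and its window: for each day, "the area under the curve (AUC) for each questionnaire will be calculated using the trapezoid method". It names the scales: "For the Karolinska, ROF, and hunger sensation scale, several measures throughout the day will be taken". The AUCs then go into a repeated-measures ANOVA across the three deficit sessions and paired t-tests against the control session. No split at the meal is stated.

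Section 2.5.1, which the deficit sessions follow, describes the second morning: "The next morning, the participants will be asked to return to the laboratory in a fasting state". Participants complete the food preference test (LFPQ) "on a computer before being served a standardized ad libitum meal (buffet-style meal", repeat it after the meal, and finish at 10:35. For the ratings it says: "Sleepiness, fatigue, and appetite will be assessed throughout the morning (i.e., 8 measures; Figure 1". Section 2.7.2 gives the same day-1 count for appetite: "i.e., 9 measures on day 0, and 8 measures on day 1". (Section 2.7.2 calls this morning day 1 and section 2.10.2 calls it day 2. Day 1 is used here.)

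Section 1.2 lists the objective as "next morning appetitive responses ([i_a_] ad libitum food intake, [i_b_] appetite sensations, [i_c_] food reward", so intake at the buffet and appetite sensations are two separate items.

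**The concern.** The buffet sits inside the window that the day-1 AUC covers, and its size is chosen by the participant. Ratings before it describe fasting appetite after a night in energy deficit. Ratings after it partly reflect the amount eaten, which is an outcome in its own right. Adding both into one area has two possible consequences:

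- If eating to satisfaction brings all sessions to a similar level, the post-meal part adds noise but little or no difference. The fasting difference is diluted.
- If hungrier participants eat more and then report less hunger, the post-meal difference has the opposite sign. The fasting difference is offset.

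These are alternatives, and the documents do not show which would occur. The second is plausible under the trial's own rationale, since sections 1.1 and 3 expect dietary deficit to raise hunger and later intake. At stake is the reading of a named secondary objective: a null pooled AUC would fit no effect on appetite as well as opposite effects before and after the meal.

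**Working it through.** **The plan's own figure.** Section 2.2.1 gives 24 subjects for 80% power with f = 0.25, correlation 0.5, four measures and sphericity 1. The noncentrality is N·m·f²/(1−ρ) = 24 × 4 × 0.0625 / 0.5 = 12, with 3 and 69 degrees of freedom. Power is 0.817; with N = 23 it is 0.797. So 24 reproduces. It was set for sleep efficiency and neither supports nor refutes this point; only n = 24 is carried forward.

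**Does the AUC span the meal?** No single sentence says so. Section 2.10.2 sets one AUC per questionnaire per day, and section 2.5.1 places eight ratings across a morning that starts fasting and continues past the buffet. Together they imply that it does.

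**Inputs that must be assumed.** The clock times of the ratings are in a figure not shown, and no SDs or correlations are given for appetite. Assume:

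- w, the pre-meal share of the morning: 0.35, 0.45, 0.55
- r, the correlation between pre-meal and post-meal within-person noise: 0.3, 0.5, 0.7
- k, the post-meal noise SD relative to the pre-meal SD: 1 or 0.5
- q, the fraction of the pre-meal effect that remains after the meal
- dz = 0.6 on the pre-meal part, which gives 80% power in a paired two-sided 5% test with n = 24 (df 23)

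**Formula.** Standardised effect on the pooled AUC relative to the pre-meal part:

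ratio = [w + q(1−w)] / √[w² + k²(1−w)² + 2rkw(1−w)]

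Power follows from the noncentral t at dz = 0.6 × ratio.

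**Central case**, w = 0.45, r = 0.5, k = 1. The denominator is √(0.2025 + 0.3025 + 0.2475) = √0.7525 = 0.867.

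- q = 0: 0.45/0.867 = 0.52, dz = 0.31, power 31%
- q = 0.5: 0.725/0.867 = 0.84, dz = 0.50, power 65%
- q = 1: 1/0.867 = 1.15, dz = 0.69, power 90%

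**Ranges over all w and r:**

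| Effect after the meal | Power, k = 1 | Power, k = 0.5 |
|---|---|---|
| none (q = 0) | 19-48% | 35-66% |
| half persists (q = 0.5) | 53-77% | 85-94% |
| all persists (q = 1) | 86-94% | 97% to over 99% |

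With k = 0.5 and q = 0.5 the standardised effect is the same before and after the meal, so pooling gains power. If the effect reverses by a quarter (q = −0.25, k = 1), power is 9-33%.

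**Cross-check with discrete ratings.** Take eight equally spaced ratings with trapezoid weights 0.5, 1, 1, 1, 1, 1, 1, 0.5 (sum 7) and an effect only before the meal. With 2, 3, 4 or 5 pre-meal ratings, the time-averaged AUC keeps 1.5/7 = 21%, 2.5/7 = 36%, 3.5/7 = 50% or 4.5/7 = 64% of the raw difference. Where the pre-meal AUC alone has 80% power, the whole-morning AUC has 9-21%, 17-39%, 29-53% or 44-64%, over common correlations of 0 to 0.9. With 4 pre-meal ratings and correlation 0.3 or 0.7, power is 58-66% if half persists, 82-88% if all persists, and 11-17% if the effect reverses by half (the upper end of that last range takes pre- and post-meal errors as independent). The pattern agrees with the formula.

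**The case against.** The strongest reply is that fasting appetite is nowhere made the target. Section 1.2 speaks of next-morning appetitive responses, section 2.7.2 has sensations measured throughout all sessions, and section 2.10.2 says that the AUC is to describe the time course over the day. A whole-morning summary that includes satiety is a legitimate answer to that objective. This stands, and the pooled AUC is therefore not an error in itself.

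The low power figures also rest on an effect confined to the fasting ratings. If the effect persists, pooling loses nothing and may gain, as the table shows. If the meal brings ratings to a floor, post-meal noise is probably small, which favours the k = 0.5 column. The rating times are unseen, so the pre-meal share is an assumption. All of this stands and limits what can be said about size.

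Nor would a null AUC stand alone: intake at the buffet is analysed separately, and the LFPQ is tested before and after the meal. A reader might infer that the AUC hides the appetite effect, or that a null result would be uninterpretable. The documents support neither.

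Finally, AUC windows are often left to an analysis plan, and segmentation is not ruled out here. But the article does name the summary and sets it per day. That is a stated choice with a better alternative close at hand, since section 2.10.2 already separates pre- and post-meal data for the LFPQ around the same meal.

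**Conclusion.** The point holds as a limitation of the stated summary. One day-1 AUC combines fasting ratings with ratings that depend partly on the amount eaten, and its result cannot show which part moved. Dilution or offset of a fasting difference is possible; complete masking is not shown.

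The loss runs from severe to none. Against 80% on the fasting part, power is about 19-66% if the effect stops at the meal and about 53-94% if half persists, and there is no loss if all of it persists. These figures rest on the assumed shares, correlations and noise ratios, not on trial data. Even if the satiety response is also of interest, the conclusion is the same: two responses need two summaries. The primary outcome and the day-0 AUC are unaffected.

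**What to change.** For day 1, pre-specify two appetite summaries: a pre-meal (fasting) AUC or mean and a post-meal AUC or mean, divided at the buffet. Analyse each with the tests already planned in section 2.10.2, and report the post-meal value beside the kcal eaten. The whole-morning AUC may stay as an additional summary, and the day-0 AUC stays as planned. State how many of the eight ratings fall on each side of the meal; where a side has too few for an area, use the mean.

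This should be written down before the data are analysed, because section 2.10.4 would have a later split reported as non-planned.

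The ratings are already collected, so nothing is added for participants. The cost is one more secondary comparison: two segments in place of one area, with the whole-morning AUC kept as description.
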